# The Qure study: Q fever fatigue syndrome – response to treatment; a randomized placebo-controlled trial

**DOI:** 10.1186/1471-2334-13-157

**Published:** 2013-03-27

**Keywords:** *Coxiella burnetii*, Q fever, Q fever fatigue syndrome, QFS, Study protocol, Treatment, Doxycycline, Cognitive behavioral therapy, Placebo

## Abstract

**Background:**

Q fever is a zoonosis that is present in many countries. Q fever fatigue syndrome (QFS) is one of the most frequent sequelae after an acute Q fever infection. QFS is characterized by persistent fatigue following an acute Q fever infection, leading to substantial morbidity and a high socio-economic burden. The occurrence of QFS is well-documented, and has been described in many countries over the past decades. However, a treatment with proven efficacy is not available. Only a few uncontrolled studies have tested the efficacy of treatment with antibiotics on QFS. These studies suggest a positive effect of long-term treatment with a tetracycline on performance state; however, no randomized controlled trials have been performed. Cognitive behavioral therapy (CBT) has been proven to be an effective treatment modality for chronic fatigue in other diseases, but has not yet been tested in QFS. Therefore, we designed a trial to assess the efficacy of long-term treatment with the tetracycline doxycycline and CBT in patients with QFS.

**Methods/design:**

A randomized placebo-controlled trial will be conducted. One-hundred-eighty adult patients diagnosed with QFS will be recruited and randomized between one of three groups: CBT, long-term doxycycline or placebo. First, participants will be randomized between CBT and medication (ratio 1:2). A second double-blinded randomization between doxycycline and placebo (ratio 1:1) will be performed in the medication condition. Each group will be treated for six months. Outcome measures will be assessed at baseline and post intervention. The primary outcome measure is fatigue severity. Secondary outcome measures are functional impairment, level of psychological distress, and *Coxiella burnetii* PCR and serology.

**Discussion:**

The Qure study is the first randomized placebo-controlled trial, which evaluates the efficacy of long-term doxycycline and of cognitive behavioral therapy in patients with QFS. The results of this study will provide knowledge about evidence-based treatment options for adult patients with QFS.

**Trial registration:**

ClinicalTrials.gov: http://NCT01318356, and Netherlands Trial Register: NTR2797

## Background

Q fever, a zoonosis caused by *Coxiella burnetii*, has been present all over the world for many years [1]. Between 2007 and 2010, the south-eastern part of the Netherlands has faced the largest outbreak of Q fever ever reported. To date, more than 4000 people have developed symptomatic disease [2], and at least up to 44,000 are estimated to have been infected [3,4]. In recent years, several studies have described the sequelae of Q fever. Acute Q fever is followed by a chronic infection in 1-5% of cases [5-7]. In addition, following acute Q fever, patients frequently report long-lasting fatigue, which often persists for more than six months [8-10]. After an outbreak of Q fever in the UK, 10 years of follow-up revealed a high percentage of persisting fatigue, with almost 20% of patients fulfilling the Centre for Disease Control (CDC) criteria of chronic fatigue syndrome, compared to 4% in healthy controls [11]. A study among abattoir employees in Australia showed that 28% of patients with proven acute Q fever fulfilled the CDC criteria of chronic fatigue syndrome five years after the infection compared to none of the seronegative controls [10]. A recent study carried out in the Netherlands among 85 patients with acute Q fever found that 59% of patients had persistent symptoms at six months after disease onset, with fatigue being the most prevalent complaint in 52% of patients. Furthermore, over 25% still had complaints after one year [12]. Another recent survey in the Netherlands among 515 patients with Q fever found that 20% had severe fatigue and an impaired health status at 12–26 months of follow-up [13]. This fatigue following acute Q fever, sometimes accompanied by several other complaints, has been designated Q fever fatigue syndrome (QFS) [14-16]. According to the recently published Dutch algorithm on QFS [14], the diagnosis of QFS can be made after a uniform diagnostic work-up. There has to be a severe fatigue, which lasts for at least six months and has a reference to an acute Q fever infection. There must be an absence of fatigue before the episode of acute Q fever or a significant increase in fatigue since the acute Q fever infection. Furthermore, it is causing significant disabilities in daily practice. Finally, chronic Q fever and other causes of fatigue, somatic or psychiatric, need to be excluded.

In the Netherlands, QFS resulted in a large incurred loss due to loss of quality of life and health-related absenteeism in the past few years [17]. Currently, extrapolating the present data, at least 800 patients suffer from QFS in the Netherlands. It is expected that Q fever will remain an endemic disease, leading to a further increase in patients with QFS, stressing the need for further research into treatment regimens for QFS.

Both acute and chronic Q fever have been extensively studied in recent years; however, less attention has been given to QFS. Although QFS is a well documented finding and has already been described in 1996 [8,10], at present there is no consensus on the pathogenetic process underlying QFS [15,18,19]. In QFS, as in chronic fatigue syndrome, persistence of live microbes has been suggested [19]. Furthermore, it is still unclear whether effective treatment for QFS is possible. So far, few studies on the effect of treatment with antibiotics on fatigue after Q fever have been done. The available studies suggest a positive effect of long-term treatment with a tetracycline on performance status [20-22]; however, these studies suffer from several limitations. So far, no controlled trials have been performed and the above long-term treatment is currently not often used in clinical care of patients with QFS. Previously, it has been shown in patients with chronic fatigue syndrome (CFS) that fatigue-related cognitions and behavior can maintain chronic fatigue [23-26]. CBT for chronic fatigue is aimed at these fatigue-related cognitions and behavior thought to perpetuate the symptoms. Several systematic reviews and meta analyses demonstrated that CBT for CFS is able to reduce symptoms and to improve function in patients with CFS [26-28]. To date, the efficacy of CBT has not been studied in patients with QFS. However, our recent clinical experience with this treatment modality in a small cohort of QFS patients shows promising results.

The primary aim of our study is to determine the effect of different treatment modalities which have been suggested to be effective for patients with QFS. In this paper we describe the protocol to assess the efficacy of two treatment strategies for QFS: long-term treatment with either doxycycline or CBT.

## Methods/design

### Study design

A randomized placebo-controlled trial (RCT), the Qure study, will be performed to determine whether long-term treatment with doxycycline or CBT will lead to a reduction of fatigue and disabilities in patients with QFS. Both treatment modalities will be compared to a placebo group. This study will be performed in the Radboud University Nijmegen Medical Centre in the Q fever outpatient clinic of the department of Internal Medicine, and in the Expert Centre for Chronic Fatigue (ECCF). QFS will be diagnosed at the Q fever outpatient clinic after a uniform diagnostic work-up according to the Dutch algorithm on QFS. Once the diagnosis is established, study eligibility will be assessed by the first author ([name]) according to specific inclusion and exclusion criteria (Tables 1 and 2). Eligible patients will be asked to participate in the Qure study after receiving verbal and written information about the study. If patients are willing to participate, written informed consent will be obtained. After inclusion, an individual study code is allocated to the participants. Results from the clinical assessment before inclusion will be used as baseline measures as well. If patients decide not to participate in this study, an attempt will be made to elucidate the reason for this, but patients are not obligated to motivate their refusal.

**Table 1 T1:** Inclusion criteria

**Inclusion criteria**^*****^	
(1)	Males or non-pregnant, non-lactating females who are 18 years or older
(2)	Laboratory-proven acute Q fever since the year 2007 and/or positive serology fitting a past infection with *Coxiella burnetii*
(3)	AND being severely fatigued, defined by scoring ≥ 35 on the subscale fatigue severity of the CIS
(4)	AND being fatigued for at least 6 months
(5)	AND being disabled because of the fatigue, defined by scoring 450 or higher on the SIP
(6)	Subject must sign a written informed consent form

* All participants have to meet the criteria for QFS according to the recently published Dutch algorithm on QFS [14]. In addition to the mentioned inclusion criteria and according to the Dutch algorithm on QFS, there has to be a severe fatigue with a reference to an acute Q fever infection. Furthermore, there must be an absence of fatigue before the episode of acute Q fever or a significant increase in fatigue since the acute Q fever infection.

Abbreviations: CIS = Checklist Individual Strength questionnaire, SIP = Sickness Impact Profile questionnaire.

**Table 2 T2:** Exclusion criteria

**Exclusion criteria**	
(1)	Fulfilling criteria for chronic Q fever^*^
(2)	Acute Q fever in the setting of a prosthetic cardiac valve or aneurysm surgery or stenting, necessitating prophylactic use of doxycycline
(3)	Pregnancy or unwillingness to use effective contraceptives during the entire study period
(4)	Imminent death
(5)	Inability to give informed consent
(6)	Allergy or intolerance to doxycycline
(7)	Somatic or psychiatric illness that could explain the chronic fatigue
(8)	Subjects who are currently enrolled in other investigational drug trials or receiving investigational agents
(9)	Receiving or having received antibiotics for > 4 weeks, potentially active against *Coxiella burnetii*, for any other reason since Q fever diagnosis
(10)	Subjects who are receiving and cannot discontinue barbiturates, phenytoin, or carbamazepine^**^
(11)	Moderate or severe liver disease (AF, ALT, AST > 3 times the upper limit of normal)
(12)	Current engagement in a legal procedure concerning financial benefits^#^

* According to the guideline chronic Q fever from the *Dutch Q fever consensus group*[29].

** These drugs may increase the metabolism of doxycycline; consequently, reducing the half-life of doxycycline.

# Temporary exclusion criterion, while current involvement interferes with the effectivity of cognitive behavioral therapy [30]. Once the appeal procedure ends, subjects can be included.

Abbreviations: AF = alkaline phosphatase, ALT = alanine aminotransferase, AST = aspartate aminotransferase.

### Study population

It is intended to include 180 patients diagnosed with QFS, equally randomized between three different treatment modalities, namely long-term doxycycline (n = 60), CBT (n = 60) or placebo (n = 60). All eligible patients directly referred to Radboud University Nijmegen Medical Centre will be asked to participate in this study. Patients with a suspicion of QFS presenting to other hospitals in the area will be referred to the Q fever outpatient clinic of the Radboud University Nijmegen Medical Centre for screening and enrollment in the study. In addition, all physicians working at specific Q fever outpatient clinics in other hospitals will be informed about the study. Patients connected to Q-uestion, a foundation for patients with Q fever, will be informed about the Qure study by newsletters, and a brief description will be available at the website of Q-uestion. Furthermore, patients who participated in previous studies on Q fever in the past few years (Q-Quest II study, ZonMw dossier number: 204004003, and The PrediQt study, ZonMw dossier number: 205520003, NL36477.091.11), will be informed about the Qure study by letter. Finally, all general practitioners in the endemic Q fever region will be informed about this study by letter.

### Ethical approval

According to the Dutch law, this study has been reviewed and approved by the Medical Ethical Review Committee of the Radboud University Nijmegen Medical Centre (registration number 2011/069, NL35755.091.11). This study will be conducted according to the principles of the Declaration of Helsinki. The inclusion of patients started in May 2011.

### Baseline assessment

After inclusion, participants will first visit the ECCF for the baseline assessment, including questionnaires and measurement with an actometer (see Figure 1). An actometer is a motion-sensing device worn at the ankle that registers and quantifies physical activity. The actometer has a piezoelectric sensor that is sensitive in three directions. Accelerations of the built-in sensor larger than a predefined threshold are considered as activity and are stored in an internal memory every 5 minutes. It is worn day and night during a period of twelve consecutive days [31]. A general physical activity score that expressed the mean activity level over this period in the mean number of accelerations per 5 minute interval will be calculated. During the period of twelve days participants rate fatigue, pain, and activity levels on a pre-scheduled Self-Observation List four times daily on a scale of 0 (not at all) to 4 (very much).

**Figure 1 F1:**
[figure not shown]
**Flowchart of trial design.** * According to the Dutch guideline Q fever fatigue syndrome [14]. Including questionnaires: general questionnaire, CIS, SIP total score. ** General questionnaire, PARS, SES28, IMQ, CBRSQ, JFCS, CAL, and SCL90. ^#^ Questionnaires used for mediation analysis: PARS, SES28, IMQ, CBRSQ, and CIS. ¥ Exclusion criteria: pregnancy; serious adverse events; AST/ALT > 5 times normal value; AF > 3 times normal value; > 10 days use of quinolon, co-trimoxazol, macroliden or tetracycline; or discontinuation of study medication > 7 consecutive days. ^ CIS, PARS, IMQ, JFCS, SIP, SES28, CBRSQ, and SCL90. Abbreviations: CIS = Checklist Individual Strength, SIP = Sickness Impact Profile, ECCF = Expert Centre for Chronic Fatigue, PARS = Physical Activity Rating, SES28 = Self Efficacy Scale, IMQ = Symptom focusing of the illness Management Questionnaire, CBRSQ = Cognitive and Behavioral Responses to Symptoms Questionnaire, JFCS = Jacobson Fatigue Catastrophising Scale, CAL = Causal Attribution List, SCL90 = Symptom Checklist 90, CBT = cognitive behavioral therapy, AST = aspartate aminotransferase, ALT = alanine aminotransferase, AF = alkaline phosphatase.

### Randomization procedure and blinding

The randomization order is created by an independent biostatistician using block-randomization. An administrative assistant with no affiliation to the project group made envelopes for individual study codes ranging from 1–180, according to the randomization list. At the end of the first visit to the ECCF, participants receive their envelope (which contains a corresponding number coherent to the individual study code) from the psychological assistant, to see to which treatment they are randomized. First, participants will be randomized between CBT and medication (ratio 1:2). Secondly, double-blinded randomization between doxycycline treatment or placebo (ratio 1:1) will be performed within the medication condition by the study pharmacist (department of Clinical Pharmacy, Radboud University Nijmegen Medical Centre). The double-blinded randomization assignment will be known to the study pharmacist only, and is available in a sealed envelope stored at the pharmacist’s office for emergency use. If the code is broken, it will render the participant not eligible. The first randomization list and second double-blinded randomization list will be made available respectively by the independent biostatistician and the study pharmacist to the principal investigator when the entire study is completed. Obviously, allocation to the CBT intervention cannot be blinded.

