### Interventions

#### Study medication

Preparation and labeling of doxycycline and placebo will be performed by the Clinical Trials Unit department of the Clinical Pharmacy of the Radboud University Nijmegen Medical Centre, and will be done according to the relevant Good Manufacturing Practice (GMP) guidelines. Study medication will be prepared as capsules with identical appearance. Participants allocated to study medication will be treated at the Q fever outpatient clinic. Participants will receive either doxycycline (200 mg once daily) or placebo (once daily), both orally administered, for a period of 24 weeks. Study medication will be provided by the first author ([name]). For safety considerations all participants in the medication condition will visit the Q fever outpatient clinic 4, 8, and 16 weeks after start of the treatment (see Figure 1). Furthermore, liver enzymes will be checked, and drug utilization will be recorded. Therefore, patients are required to bring the study medication to all visits. In addition, blood samples drawn 8 weeks after start of treatment will be stored by the study pharmacist, who performed the double-blinded randomization. Eventually, doxycycline levels will only be determined in participants receiving doxycycline, and results will be kept secret until the entire study is completed. After completion, it is known whether doxycycline levels were sufficient to sort out effect [32]. Participants will be excluded in case of: serious side effects; aspartate aminotransferase (AST)/alanine aminotransferase (ALT) levels more than 5 times the upper limit of normal; alkaline phosphatase (AF) levels more than 3 times the upper limit of normal; more than 10 days use of antibiotics potentially active against *C. burnetii* (co-trimoxazol, quinolon, macrolides or tetracyclines); or discontinuation of study medication for more than 7 consecutive days.

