### Withdrawal of individual participants

Participants are informed that they can stop participating in the study at any time, without consequences. Although participants will be asked for the reason for discontinuation, giving a reason for withdrawal is not obligatory. The investigator can decide to withdraw a participant from the study in case of medical urgency. In addition, study medication will be stopped in case of pregnancy, and the participant will be withdrawn. According to the Intention To Treat (ITT) principle the analysis will be based on the initial treatment intent. Therefore, in case of discontinuation, all efforts will be made to complete and report the observations as thoroughly as possible. A complete final evaluation in accordance to the study protocol end-of-therapy study visit will be performed if the withdrawn participant agrees. Because of absence of an evidence-based treatment for QFS, other treatment options for QFS in regular health care for withdrawn participants in the CBT group are not available. Long-term doxycycline treatment is not offered, because of possible (serious) side-effects and a lack of evidence so far.

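### Post-randomisation events make participants excluded or not eligible, which the plan does not reconcile with its intention-to-treat and completer rules

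*Protocol article*

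**What the plan says.** Three places in the protocol article attach a loss of status to events that can only happen, or are only counted, after randomisation.

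- **Randomization procedure and blinding**, on emergency unblinding: "If the code is broken, it will render the participant not eligible".
- **Study medication**: "Participants will be excluded in case of: serious side effects; aspartate aminotransferase (AST)/alanine aminotransferase (ALT) levels more than 5 times the upper limit of normal". The list goes on to an alkaline phosphatase limit, "more than 10 days use of antibiotics potentially active against" *C. burnetii*, "or discontinuation of study medication for more than 7 consecutive days".
- **Figure 1 legend**: "Exclusion criteria: pregnancy; serious adverse events; AST/ALT > 5 times normal value; AF > 3 times normal value", followed by the same antibiotic and off-drug rules.

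Two other places point the other way.

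- **Withdrawal of individual participants**: "According to the Intention To Treat (ITT) principle the analysis will be based on the initial treatment intent". The section then asks for observations to be completed as far as possible after discontinuation, with the full end-of-therapy evaluation if the withdrawn person agrees.
- **Statistical analysis**: ITT underlies every analysis, and the primary analysis uses completers. A completer is anyone with the measurements taken after the intervention. That definition has no condition on adherence, toxicity, other antibiotics or unblinding.

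**The concern.** Eligibility is settled before randomisation. A code break, a toxicity event or an interruption of dosing comes later and may be a consequence of the allocated treatment. Calling such a participant *not eligible* or *excluded* invites whoever builds the dataset to drop that person, while the withdrawal and statistical sections would keep anyone who was assessed. Two analysts following different sections could produce different primary datasets.

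The exposure is uneven across arms. A code break and time off study medication can occur only in the two medication arms. The clinic visits at weeks 4, 8 and 16, with liver-enzyme checks and recording of drug use, are scheduled only there. The CBT section has no matching rule. Within the medication arms, serious side effects, enzyme rises and stopping the capsules may be more frequent on doxycycline than on placebo.

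The planned check on missing data would not reliably expose a problem. It is triggered only by a significant result, so a null finding affected by exclusions would go unexamined.

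**Working it through.** **1. What each section implies for a participant who meets one of these events and still attends at week 24**

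| Section | Implied status |
|---|---|
| Randomization procedure and blinding (code break) | not eligible |
| Study medication; Figure 1 legend | excluded |
| Withdrawal of individual participants | evaluated if willing; analysed as allocated |
| Statistical analysis | completer, analysed as allocated |

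No sentence links the first two rows to the last two. The withdrawal section names the participant's own choice, medical urgency and pregnancy, and speaks generally of discontinuation. It does not mention a code break.

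**2. The two lists differ.** Study medication refers to serious side effects; the legend refers to serious adverse events. These are not the same thing, because the Adverse events section counts events whether or not they are related to treatment. The legend also lists pregnancy, which the Study medication list omits, although the withdrawal section covers it.

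**3. The plan's design effect.** The Power calculation section takes 50 evaluable per arm and a baseline correlation of 0.34.

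- Design factor: 1 − 0.34² = 0.8844. Effective n: 50 / 0.8844 = 56.5 per arm.
- Two-sided t-test, alpha 0.05, power 0.80: detectable effect 0.534 at n = 56 and 0.531 at n = 56.5. The stated 0.53 is reproduced.

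**4. Size of bias if these participants are dropped.** The article gives no event rates or outcome gap, so all of these inputs are assumptions. Let a fraction f of an arm be dropped, and let those dropped score k SD worse than those kept. The full-arm mean is then the retained mean plus f × k, so dropping them makes the arm look better by f × k. Hence:

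- doxycycline versus placebo: bias in favour of doxycycline = (f_dox − f_plac) × k
- CBT versus placebo, with no one dropped from CBT: bias against CBT = f_plac × k

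The type I error below is two-sided, with 60 × (1 − f) retained per arm and SE = √0.8844 × √(1/n_dox + 1/n_plac).

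| f_dox / f_plac | k | Doxycycline vs placebo (SD) | Type I error | CBT vs placebo (SD, against CBT) |
|---|---|---|---|---|
| 10% / 5% | 0.5 | 0.05 × 0.5 = 0.025 | 5.2% | 0.025 |
| 10% / 5% | 1.0 | 0.05 × 1.0 = 0.05 | 5.9% | 0.05 |
| 20% / 10% | 0.5 | 0.10 × 0.5 = 0.05 | 5.8% | 0.05 |
| 20% / 10% | 1.0 | 0.10 × 1.0 = 0.10 | 8.4% | 0.10 |
| 20% / 5% | 0.5 | 0.15 × 0.5 = 0.075 | 6.9% | 0.025 |
| 20% / 5% | 1.0 | 0.15 × 1.0 = 0.15 | 12.9% | 0.05 |

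If those dropped did better than those kept, the signs would reverse.

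**5. Power, if exclusions came on top of the planned drop-out.** At an effect of 0.53, doxycycline versus placebo has 79.8% power with 50 per arm. It has 76.5% with 10% of doxycycline and 5% of placebo excluded (45 and 47.5 left), 72.8% with 20% and 10% (40 and 45), and 70.3% with 20% in both (40 and 40).

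**The case against.** The best defence is that no section says anyone is excluded *from the analysis*. The Study medication list may mean only that study treatment ends. Read with the withdrawal and statistical sections, a participant taken off the drug who attends at week 24 would then be a completer in the randomised arm, and there would be no bias. This is a fair reading. It means that a reader who infers that the plan removes these patients, or that both contrasts have lost the protection of randomisation, goes further than the text does.

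A reader might also infer that the rules apply to the medication arms alone. That is certain only for the code break and time off drug. For the other items it rests on where the list is placed and where monitoring is scheduled. The flowchart itself is not available here, pregnancy and serious adverse events can occur in any arm, and the withdrawal section refers to withdrawn CBT participants.

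The magnitudes are assumed throughout. The article describes doxycycline as well characterised, with side-effects beyond gastrointestinal complaints and photosensitivity being rare, so the higher exclusion rates may not arise. Nor does it say that exclusions would add to the 20% drop-out; they may be part of it.

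What the defence does not remove is the contradiction. *Not eligible* cannot describe someone already randomised and treated, a code break is not clearly covered by the withdrawal section, and the favourable reading has to be assembled from separate sections that never refer to these rules.

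**Conclusion.** The point holds as an unreconciled contradiction about who is in the primary analysis. The exclusion wording in Randomization procedure and blinding, Study medication and the Figure 1 legend does not fit the ITT statements and completer definition elsewhere.

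Bias is conditional on applying that wording literally. Under the illustrative rates it is 0.025 to 0.15 SD for doxycycline versus placebo, which is about 5% to 28% of the design effect (0.025 / 0.53 and 0.15 / 0.53), and 0.025 to 0.10 SD against CBT in the other contrast. These figures show scale only: the event rates and the outcome gap are assumptions, and the true size is unknown. With modest rates the effect is small. The documents support a correction that should be made, not a finding that the trial's comparisons are invalid.

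**What to change.** In Randomization procedure and blinding, Study medication and the Figure 1 legend, replace the terms *excluded* and *not eligible* with wording to this effect: the listed events, including a code break, do not by themselves end follow-up or remove a participant from the randomised arm, and anyone with a week-24 assessment counts as a completer in the primary analysis.

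Reconcile the Study medication list with the legend (serious side effects against serious adverse events; pregnancy) and state which arms the list covers. None of this requires changing a clinical stopping limit, and no view is taken on those limits. A supportive per-protocol set built from these events is optional and can be left to the SAP.

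The cost is a few sentences, plus outcome assessments for participants who stop, which the withdrawal section already intends. The change should be made before the allocation lists are released.
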